### **10.1.5 Definitions of adverse events**

*Probable* - A clinical event, including laboratory test abnormality, with a reasonable time sequence to administration of the drug, unlikely to be attributed to concurrent disease or other drugs or chemicals, and which follows a clinically reasonable response on withdrawal. Rechallenge information is not required to fulfil this definition.

*Possible* - A clinical event, including laboratory test abnormality, with a reasonable time sequence to administration of the drug, but which could also be explained by concurrent disease or other drugs or chemicals. Information on drug withdrawal may be lacking or unclear.

*Remote* - A clinical event, including laboratory test abnormality, with an improbable time sequence to drug administration and in which other drugs, chemicals, or underlying disease provide a plausible explanation.

*None* - A clinical event for which sufficient information exists to indicate that the aetiology is unrelated to the suspected drug. This may include: (1) the existence of a clear alternative explanation (for example, mechanical bleeding at surgical site); or (2) non-plausibility (for example, the subject is struck by an automobile at least where there

is no indication that the drug caused disorientation that may have led to the event, or cancer developing a few days after drug administration).

*Not assessable* - A clinical event, including laboratory test abnormality, reported as an adverse reaction, about which more data is essential for a proper assessment or the additional data is under examination.

Factors to be considered include the following:

1. The temporal sequence from drug administration: The event should occur after the drug is given. The length of time from drug exposure to event should be evaluated in the clinical context of the event.
2. Recovery on discontinuation (dechallenge), recurrence on re-introduction (rechallenge): Individuals' response after drug discontinuation (dechallenge) or individual's response after drug re-introduction (rechallenge) should be considered in the view of the usual clinical course of the event in question.
3. Underlying, concomitant, intercurrent diseases: Each report should be evaluated in the context of the natural history and course of the disease being treated and any other disease the individuals may have.
4. Concomitant medication or treatment: The other drugs the individual is taking or the treatment the individual receives should be examined to determine whether they might be recognised to cause the event in question.
5. Known response pattern for this class of drug: Clinical/preclinical.
6. Exposure to physical and/or mental stresses: The exposure to stress might induce adverse changes in the recipient and provide a better, more logical explanation for the event.
7. The pharmacology and pharmacokinetics of the test drug: The pharmacokinetic properties (absorption, distribution, metabolism and excretion) of the test drugs the individual is taking, coupled with the individual's unique pharmacodynamics should be considered.

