### **5.4 Safety Monitoring Board**

Given the short duration of this study and the fact that just a single immunization will be given on study day 0, a safety monitoring board (SMB) is not deemed suitable for this study. The Principal Investigator will monitor all serious adverse events and if considered to be related to study medication this will be notified to the ethics committee.

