## **8. STUDY PROCEDURES AND EVALUATIONS**

### **8.1 Assessment periods**

One immunisation will be performed on Day 0 (Visit 1). Although the final study visit takes place 4 weeks after immunization, the total follow up period may be up to 12 months with a provision for a telephone call to the subject during this period to ascertain any new medical events that might have occurred during this interval.

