### **9.6 Safety analysis**

All adverse events will be summarized and listed with a detailed description, using the MedDRA dictionary. Frequencies of adverse events (number of patients with the event, number of mentions of the event and percentage of patients exhibiting the event) for each vaccine formulation and immunisation route will be given for all adverse events. Adverse events will be summarized by vaccine formulation and immunisation route, body system and relationship to study drug and severity. In addition, listings will be prepared for adverse events leading to treatment discontinuation and for SAEs.

The vital signs (sitting blood pressure, heart rate and temperature) will be presented with summary statistics over the visits and for the change from baseline to endpoint. Individual laboratory variables over the visits and the change from baseline to endpoint will be listed with summary statistics for each dose level. The frequencies of laboratory values below, within and above the relevant normal ranges will be given. The baseline and endpoint laboratory variables will be presented using a contingency table to investigate any range changes. The abnormal and clinically significant laboratory variables will be presented for each patient over the assessments.

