### **10.1.4 Methods of recording and assessing adverse events**

All adverse events must be documented in the section of the CRF reserved for this purpose and not in remarks elsewhere in the CRF. The following aspects must be recorded

- The onset.
- Where applicable, the end of the adverse event.
- A description of the adverse event.
- Any factors considered as possibly promoting the occurrence of the adverse event.
- Concomitant medication.

An assessment by the investigator of the causality; the decisive factor in the documentation is the temporal relationship between the adverse event and the study drugs. The following judgments of the causal relationship are possible: none, remote, possible, probable and not assessable. If, in any individuals, the same adverse event occurs at several investigational times, then the adverse event in question must be documented and assessed anew each time.

Participants will be monitored by study staff for 30 min after immunization for any immediate adverse events and by the subjects themselves using a symptom diary for 28 days post immunization. Participants will be instructed to assess specific injection site adverse events (redness, swelling, warmth, tenderness, pain with arm movement) and systemic adverse events (chills, headache, muscle aches, fatigue, nausea, vomiting, diarrhoea, joint pain), all reports of other adverse events will be collected and categorized by body system. Adverse events will be collected by study personnel at each visit.

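### The definition of a probable causal link requires a response on withdrawal, which does not apply to a single-dose vaccine and leaves clear reactions without a well-fitting category

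*Protocol*

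**What the plan says.** Section 10.1.4 limits the investigator to five ratings: "The following judgments of the causal relationship are possible: none, remote, possible, probable and not assessable". Nothing ranks above *probable*.

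Section 10.1.5 defines them. *Probable* needs a reasonable time sequence and an event "unlikely to be attributed to concurrent disease or other drugs or chemicals, and which follows a clinically reasonable response on withdrawal". It then adds: "Rechallenge information is not required to fulfil this definition". *Possible* has the same timing element, "but which could also be explained by concurrent disease or other drugs or chemicals", and accepts that withdrawal information may be missing.

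Section 5.4 fixes the exposure: "just a single immunization will be given on study day 0". Section 8.1 agrees.

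The ratings are used in section 9.6: "Adverse events will be summarized by vaccine formulation and immunisation route, body system and relationship to study drug and severity".

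**The concern.** The withdrawal condition assumes a treatment that continues and can be stopped. After one injection nothing can be stopped, yet the condition is joined by *and* to the other requirements for *probable*. The waiver that follows covers rechallenge only. The allowance for missing withdrawal information sits under *possible* and not under *probable*, so the text does not excuse its absence for the higher rating.

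At stake is whether the relationship column in the section 9.6 summary means the same thing from one rater and event to the next. The rating is made when the event is recorded. A later analysis can combine categories, but it cannot recover what a rater would have recorded under a clear definition.

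**Working it through.** The plan states no figure on this point and no arithmetic applies. The check sets a test event against each definition in 10.1.5.

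**Test event.** Injection-site redness on the day of vaccination, with no concurrent illness or other drug to explain it, after the single dose fixed in 5.4 and 8.1.

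**Literal reading** (withdrawal means stopping treatment):

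- *Probable*: timing is met and absence of a likely alternative is met. Response on withdrawal cannot be met. Fails.
- *Possible*: timing is met, but no alternative explanation exists. Fails.
- *Remote*: needs improbable timing. Fails.
- *None*: needs enough information to show that the event is unrelated. Fails.
- *Not assessable*: needs essential data to be outstanding. None are. Fails.

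Result: 0 of 5 categories fit.

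**Lenient reading** (resolution after the single exposure counts as the response):

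- Redness that has faded when rated: *probable* fits.
- A reaction still present when rated: *probable* is not yet met, and *possible* still fails for want of an alternative cause. *Not assessable* could be argued while resolution is awaited.

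The unresolved case is foreseeable. Section 5.1.4 looks for granuloma and skin breakdown, and 7.8.3 lists autoimmune disease among the events to be treated as serious. Section 10.2 sets a one-working-day limit for reporting serious events, and resolution may not be known by then.

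**Where the rating is used:**

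- 9.6, summary by relationship to study drug: uses the scale.
- 9.6, proportions with a reaction, estimated by group, time window and severity, with percentages compared by Fisher's exact test: no causality rating is named.
- 9.1.1, primary variable (b): concerns how often events occur and how severe they are, not relatedness.
- 10.1.2, 10.2 and 12.1, reporting of serious events: no relatedness condition.
- 5.4: one sentence makes notification conditional, "if considered to be related to study medication this will be notified to the ethics committee".

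**The case against.** The strongest reply is that a sensible investigator would not be stuck. Section 10.1.4 calls timing the decisive factor. Section 10.1.5 lists dechallenge as one of seven factors to consider, to be judged against the usual course of the event, and another factor is the known response pattern of the class. Redness that appears after the injection and fades would readily be called *probable*. If not, *possible* tolerates missing withdrawal information and is the natural fallback.

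Much of this stands. It means that a reader should not infer that no event in any of the six groups can be rated *probable*, or that clear reactions lose every related rating. Both follow only on the literal reading. The reply does not repair the definition, however. The clause remains mandatory as worded, the lenient reading does not help an event that is unresolved when rated, and 10.1.4 and 10.1.5 pull raters in different directions.

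A second reply is that little depends on the scale. That also largely stands. From 5.4 a reader might infer that serious events could go unreported because of a poor causality rating. The documents do not support this: 10.1.2, 10.2 and 12.1 require reporting without a relatedness test, and 5.4 itself asks only whether the event is considered related, not whether it is *probable*. The difference between 5.4 and those sections is a separate inconsistency that must be reconciled.

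A third reply is that the same definitions apply in all six groups and that 5.2 provides a blinded adjudicator where an adverse effect requires assessment. This stands too. Nothing in the protocol shows an effect that differs between groups.

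**Conclusion.** The definition is wrong as written for a one-dose trial. The likely consequence is uneven grading, or a shift from *probable* to *possible*, in one descriptive summary, with unresolved events most exposed. A table that combined those two categories would absorb that shift, but not events placed in *not assessable*.

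The size cannot be given as a number. It depends on how raters read the clause and on how many reactions are unresolved when rated, and the protocol states neither. It would be too strong to say that the safety results are distorted, because the main reactogenicity comparisons and primary variable (b) do not rest on the scale.

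The conclusion assumes that raters apply 10.1.5 as written and that no other guidance disapplies the withdrawal clause. It is a minor to moderate wording defect, worth correcting because the correction is nearly free.

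**What to change.** In 10.1.5, delete the withdrawal clause from *probable*, or add that it does not apply to a vaccine given once. *Probable* then rests on plausible time from injection and no likely alternative cause. In the list of factors, mark factor 2 (dechallenge and rechallenge) as not applicable.

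The cost is a wording amendment and a matching line in the case report form guidance. No new data, visits or staff are needed. Which ratings are pooled as related, and whether solicited local reactions are taken as related by default, can be left to the statistical analysis plan or that guidance.

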#### **10.1.6 Intensity (severity) of the adverse event**

In addition to assessing the relationship of the administration of the investigational product to adverse events, an assessment is required of the intensity (severity) of the event. The following classification should be used for events which do not have a grading in the CTC categories:

*Mild*: An adverse event which is usually transient in nature and generally not interfering with normal activities. The individuals may experience slight discomfort.

*Moderate*: An adverse event causing some limitation of usual activities that is sufficiently discomforting.

*Severe*: An adverse event causing inability to carry out usual activities. The individuals may experience intolerable discomfort or pain.

*Life-threatening*: An adverse event presenting an immediate risk of death from the event as it occurred.

#### **10.2 Procedures for reporting SAEs**

Any clinical adverse event or abnormal laboratory test value that is serious (including death, overdose or congenital anomaly) occurring during the course of the study, irrespective of the treatment received by the individuals, must be reported by the

Investigator to the Sponsor, and where relevant the Site Ethics Committee within one working day of knowledge of occurrence.

Following a report by phone, written information has to be sent by fax. For all reports, the form “Alert Report for SAEs” must be used. The adverse event itself must be documented and medically assessed by the investigator and the outcome described in the section of the CRF reserved for this purpose. Such preliminary reports will be followed by detailed descriptions later that will include copies of hospital case reports, autopsy reports and other documents when requested and applicable. This additional information will be requested, if necessary, by the responsible monitor within 5 days of receipt of the alert report. This is to ensure that the initial reporting of serious adverse reactions is made to regulatory authorities within the required time period. For a follow-up report to the authorities, the monitor may be required to collect further information for a final evaluation of the case. Reporting to the Health Authorities will be the responsibility of the Investigator.

### **10.3 Monitoring of individuals with adverse events**

Each individual must be carefully monitored for adverse events. Assessment must be made of the seriousness, intensity and relationship to the administration of the study drug. In case of an adverse event, the investigator will decide if the study will be continued or terminated for the individuals. In case of an SAE, the study drug will be stopped, the individuals will receive appropriate treatment, and the individuals will be closely observed until reversal of the event and stabilization of the subject.

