**9.3 Statistical analysis**

A descriptive analysis will be performed. All variables will be analysed descriptively. The safety analysis will be performed for the safety population. The efficacy analysis will be performed for the PPP population.

Protocol violations will be listed by patient. Protocol violations include the following:

- (a) Non-compliance of the inclusion and exclusion criteria.
- (b) Non-permitted concomitant medication
- (c) Scheduled visit occurring outside of visit window

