## **10. DRUG SAFETY**

### **10.1 Definition of adverse events and SAEs**

#### **10.1.1 Adverse event**

An adverse event is defined as:

Any untoward medical occurrence in an individual or clinical investigation subject who has been administered a pharmaceutical product and which does not necessarily require a causal relationship with the treatment. An adverse event can therefore be any unfavourable and unintended sign (including an abnormal laboratory finding, for example), symptom, or disease temporarily associated with the use of a medicinal product, whether or not considered related to the medicinal product.

Specifically, adverse events include:

1. All unfavourable changes in general condition.
2. All subjective or objective symptoms.
3. All concomitant diseases or accidents.
4. All clinically relevant changes in laboratory parameters.

Post-immunisation adverse events will be specifically defined as those adverse events occurring in the first 28 days post-immunisation. However, adverse event data will continue to be collected for the duration of the study follow-up period of 1 year post-immunisation

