### **11.5 Discontinuation of study subjects**

According to the Declaration of Helsinki, subjects may withdraw from the study at any time for any reason. The reason for withdrawal will be recorded in the clinical records and the CRF. Potential reasons for withdrawal are:

- a. Significant adverse events, for example:
  - i. Serious toxic or allergic reaction.
  - ii. Intercurrent diseases.
  - iii. Aggravation of a concomitant disease.
  - iv. Serious laboratory abnormality.
- b. Withdrawal of consent.
- c. Protocol violations.

Patients who are withdrawn from the study should undergo the follow-up procedures as specified for early termination of the study.

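### Section 10.3 lets the investigator end a subject's participation after any adverse event, although no treatment remains to stop, so the rest of the scheduled safety follow-up can be lost

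*Protocol*

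**What the plan says.** **Dosing.** Section 5.4 notes that "just a single immunization will be given on study day 0", and section 8.1 agrees.

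**Ending participation.** Section 10.3 says: "In case of an adverse event, the investigator will decide if the study will be continued or terminated for the individuals". It sets no grade, criteria or relation to further dosing. The next sentence begins "In case of an SAE, the study drug will be stopped", though no dose is left. It ends by requiring that "the individuals will be closely observed until reversal of the event and stabilization of the subject".

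**Withdrawal.** Section 11.5 opens with the subject's right to leave at any time. It then lists potential reasons, including significant adverse events and protocol violations, and closes: "Patients who are withdrawn from the study should undergo the follow-up procedures as specified for early termination of the study". Section 8.6 defines those procedures as an examination with vital signs, blood tests where indicated, a sample for influenza antibodies and T-cells, and adverse event recording. It specifies nothing afterwards.

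**Planned safety follow-up.** Section 10.1.4 sets a 28-day symptom diary and collection of adverse events at each visit. Section 4.1.1 has a Day 28 visit for all subjects and one optional telephone call between Days 185 and 365. The tolerability and safety part of section 5.1 collects unsolicited events for 6 months, whereas section 10.1.1 says "adverse event data will continue to be collected for the duration of the study follow-up period of 1 year post-immunisation".

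**The concern.** In a repeat-dose trial, a rule of this kind can spare a subject further exposure. Here the exposure is complete on Day 0, so ending participation withholds no vaccine. Its effect on the trial is to stop data collection. The protocol does not separate stopping treatment from leaving follow-up.

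Safety is a primary endpoint. If participation ends because of an adverse event, the missing data depend on the outcome being measured. The subject stays in the safety population (section 9.2.1 takes everyone who was dosed), so later events that nobody sees count as no event. Section 5.2 says the staff giving the vaccine cannot be blinded, because the adjuvanted product is cloudy. Section 7.7.3 allows the investigator to give it. The decision under section 10.3 may therefore be taken by someone who knows the arm, and the loss could then differ between arms. An analysis plan cannot recover data that the site was allowed to stop collecting.

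**Working it through.** The point is procedural, so the main check sets the sections side by side. The arithmetic only shows scale.

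**1. What survives when participation ends after an adverse event**

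| Item | Continues? | Source |
|---|---|---|
| Examination, vital signs, adverse event recording | Once, at termination | 8.6, 11.5 |
| Antibody and T-cell sample | Once, at termination | 8.6 |
| Observation of a serious event | Until reversal and stabilization | 10.3 |
| Clinically significant unexplained laboratory abnormality | Until normal and/or explained | 10.4 |
| Remaining diary days | No provision | 10.1.4 |
| Day 28 visit and sample | No provision | 4.1.1 |
| Later safety contact | No provision | 4.1.1, 5.1, 10.1.1 |

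The gap is therefore the remaining scheduled follow-up, mainly after non-serious events. It also covers new events arising after the one that led to termination.

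**2. Share of each period left unobserved**

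Formula: 1 − d/L, where d is the day of termination and L the length of the period. The days d = 7 and d = 14 are assumptions, and 6 months is taken as 182 days.

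- 28-day window (10.1.1): 1 − 7/28 = 75%; 1 − 14/28 = 50%.
- 6 months (5.1): 1 − 7/182 = 96.2%; 1 − 14/182 = 92.3%.
- 1 year (10.1.1): 1 − 7/365 = 98.1%; 1 − 14/365 = 96.2%.

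The last two lines describe nominal collection periods. After Day 28 the schedule holds only one optional call, so the firmer loss is the diary and the Day 28 visit.

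**3. Effect on the antibody endpoint**

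Section 2.1 sets the primary titre at 21–28 days. Section 9.2.2 admits anyone with a baseline and one post-baseline antibody value, and section 9.4 allows the last value to be carried forward. A Day 7 termination sample qualifies, 21 − 7 = 14 days before the earliest time in section 2.1. The subject usually stays in the analysis, but with a titre taken at the wrong time. If titres are still rising then (an assumption), the value is too low.

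**4. Group size**

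Section 9.7 wants at least 50 per group after 20% dropout. 50/(1 − 0.20) = 62.5, rounded up to 63, and the plan uses 65, so its figure is reproduced with a small margin. 65 × 0.80 = 52, a reserve of 2. The minimum is missed once the loss of final samples exceeds 15/65 = 23.1%.

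The documents give no rate for withdrawals under section 10.3. Suppose they come on top of the 20% and all fall before Day 28. With an extra proportion w, 65 × (0.80 − w) subjects per group have a final sample:

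- w = 1%: 51.4
- w = 3%: 50.1
- w = 5%: 48.8
- w = 10%: 45.5

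If the 20% already covers them, the 52 is unchanged.

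**The case against.** Much can fairly be said on the other side.

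- **A reader might infer that safety follow-up is cut off altogether.** The documents do not support that. Serious events, significant laboratory abnormalities and the termination assessment are all covered.
- **A reader might infer that the Day 28 endpoint loses these subjects.** They normally stay in through the Day 7 or termination sample. The problem is mainly one of timing.
- **A reader might infer that a late visit can end participation**, because section 9.3 counts "Scheduled visit occurring outside of visit window" as a violation and section 11.5 lists violations as a reason for withdrawal. Section 9.3 only lists violations by patient, and section 11.5 does not say that the investigator withdraws anyone. Such withdrawals also need not involve a reaction.
- **Long-term loss is limited.** The late call is optional and section 11.9 sets a minimum of one month, so late events could be missed in any subject.
- **Blinding is partly protected.** Section 5.2 gives adverse effects that need assessment to a blinded adjudicator. No section says that the person deciding under section 10.3 saw the vaccine.
- **The power is discretionary**, and after one injection there may be little reason to use it.

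All of this stands, and it narrows the point. It does not supply a sentence that keeps a subject in the diary and the Day 28 visit after the investigator ends participation for a non-serious event. The adjudicator assesses the event; section 10.3 leaves the termination decision to the investigator.

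**Conclusion.** The point holds in a limited form. Section 10.3 permits, but does not require, participation to end after any adverse event, without criteria and with no dose left to stop. What is then lost is the rest of the scheduled safety follow-up, mainly after non-serious events, and a correctly timed Day 28 titre.

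The loss would depend on having reacted. Whether it would differ by arm rests on the possibility, open under sections 5.2 and 7.7.3, that the deciding investigator knows the allocation. Its size cannot be estimated from the documents. The 75% figure assumes termination on Day 7, and the group-size figures assume extra withdrawals of 1–10%. The conclusion depends on neither. This is an inexpensive improvement worth making, and not a flaw that invalidates the design.

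**What to change.** Reconcile sections 10.3, 11.5 and 8.6 with the single-dose design and with the adverse event collection periods in sections 5.1 and 10.1.1, which also disagree with each other (6 months against 1 year).

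State that, for data collection, an adverse event or protocol violation after vaccination does not by itself end follow-up. Subjects who still consent keep the diary, the Day 28 visit and sample, and whatever later safety contact the protocol provides for all subjects. State also that clinical care remains with the investigator and that the right to withdraw is unchanged. This concerns which data are collected and sets no clinical rule.

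The cost is a few sentences of protocol wording and the completion of already planned contacts for a few more subjects.
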